## Methods

**Study design: **The protocol of this randomized controlled trial study has been approved by the Institutional Review Board of Babol University of Medical Sciences (IR.MUBABOL.HRI.REC.1396.179). 

**Study setting: **This study will be conducted at the Infertility and Reproductive Health Center affiliated to Babol University of Medical Sciences and at the urology clinic. 

**Sample size: **The trial is powered to detect an effect size of d ≥0.70 as statistically significant in a two-tailed test with α=0.05 and power of 0.80 with N=26 per condition. As there is the possibility that some patients do not complete the study, we will include 30 patients in Carob and vitamin E groups.

**Participants: **Male partners of couples attending the infertility center of Babol University of Medical Sciences will be included in the study. The proposed sample size is 60 men with teratospermia and oligozoospermia with 30 men in the experimental group taking Carob syrup and 30 men in the comparison group and receiving vitamin E. 

**Eligibility criteria: **The eligibility of each included subject will be confirmed by the urologist. Patients eligible for the trial must comply with all of the following at randomization:

20-45 years of age, who had complained of infertility for at least 12 months, and had no history of surgical or medical treatments for infertility.Having a BMI less than 30.Uncertain oligo-spermatozoa due to WHO criteria (sperm concentration less than 15 million per ml, type A motility less than 25%, and type B mobility Less than 50%, normal morphology less than 15%).Not smoking, drinking alcohol, and addiction to substance. Lack of systemic illness diseases, such as diabetes and thyroid disease, cerebrovascular disease and had no history of chemotherapy.Naturally occurring gonadotropins, testosterone and prolactin 

Lack of history of vasectomy or obstructive azoospermia. Patients with recurrent or residual varicocele, and history of cryptorchidism or Azoospermia and chromosomal abnormalities such as kleinfelter's Syndrome are not enrolled in the study.

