**Exclusion Criteria:**

Genital tract infection.The use of antioxidant supplements in the last three months and during the study.The use of chemical drugs during the study.Having severe physical activity. Hypogonadism or pituitary abnormalities.

**Recruitment: **In the run-in phase of the study, a member of the research team (reproductive health researcher) and urologist present at Fatemezahra Infertility Clinic 3 days in a week. The investigators will inform the participants of all aspects pertaining to participation in the study and will screen all the patients for the eligibility criteria at the time of admission. Subjects` screening will be continued until the target population is achieved. Participants will be free to withdraw any time during the study, and this will not affect their clinical treatment.

**Pre-randomization data: **At the initial visit, baseline clinical demographics and a complete medical history will be obtained through a clinical interview, including age, occupation, body mass index, cigarette use, alcohol intake, medical history, drug history and a working clinical diagnosis. A physical examination will be performed in all who have a disorder in the number, motility or morphology of the sperm to identify any potentially eligible infertile men for the study. The criteria for choosing patients with disorders in terms of sperm count (oligospermia) abnormal morphology (teratospermia) and reduced sperm motility (asthenospermia) as well as the statistical results of the semen analysis are based on the WHO criteria (14). After the urologist determines that the patient is eligible for recruitment, all eligible participants will be asked to sign a written consent form before being enrolled in the study.

**Blinding: **The researchers performing and analyzing data from the semen samples, endocrine tests, and biomarker analysis (outcomes assessor) will be blinded to the participant grouping. 

**Allocation (method & allocation concealment mechanism): **The block randomization method will be used to randomize patients into groups that result in equal sample sizes to ensure a balance across groups over time.

Before initiation of the run- in phase of the study, two 60- sets of random numbers will be created by a member of the research team not involved in recruitment. 15 blocks with size of 4 and combination of A for the carob and B for vitamin E group will be prepared.

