**Assessments:**						
FSH,LH,Prolactin, MDA Testosterone, TAC level						X
Semen analyses						X
**Adverse events**			X	X	X	X

**Data Monitoring: **Two researchers from BUMS not involved in the study and chosen by the university will monitor the data and supervise the conduct of the study.

**Intervention: **Patients will be assigned (1:1) to receive Carob syrup twice a day or vitamin E (comparison group) 100 mg once a day for 3 months. The Carob pods will be purchased from herbal market in Tehran and after identification and confirmation by botanist will be powdered and extracted by decoction in water (100 gram Carob, (traditional dosage) in 500 ml water). Then, after filtration, will be mixed with 500 ml USP syrup. Each patient will use 15 ml of Carob syrup/day (divided ×2) (~ dosage in traditional medicine). For all patients, a spermogram is performed first. Three months after the treatment, the spermogram and blood samples were taken from the two groups. The main consequence of the study is to improve the spermogram test and the secondary outcome of each of the parameters of prolactin, FSH, TAC, MDA and testosterone. During the initial visit where recruitment of the study occurs, the participants will be prescribed the medication. It is initially prescribed for two weeks. One week later, a telephone interview will be conducted to review the side effects and arrange an early appointment with the patient’s request. Two weeks later, the patient will received the remaining medications and adherence to treatment will be assessed (Figure 1).

**Follow-up: **Participants will be monitored monthly for signs or symptoms of adverse effects. One month later, the participants will be reviewed in the clinic and a possible side effect check list will be conducted. To prevent attrition and to assess adherence to treatment, telephone interviews will be conducted again at 2 months from administration of the drug. 3 months after intervention and upon completion of the drugs, all participants will be checked in the infertility clinic, semen analysis will be performed according to the standard clinic protocols for the sperm count, motility and morphology and serum samples will also be collected in order to evaluate markers of oxidative stress and reproductive hormones (Figure 1).

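### Every block has the same size of 4 while the recruiting researcher can see past treatments: used in serial order, the blocks reveal on average one third of allocations in advance

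*Protocol article*

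**What the plan says.** All references are to the Methods of the protocol article.

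- **Block scheme (Allocation).** "15 blocks with size of 4 and combination of A for the carob and B for vitamin E group will be prepared". The section gives two reasons for blocking: equal group sizes, and arms kept level as recruitment proceeds.
- **Ratio and products (Intervention).** "Patients will be assigned (1:1) to receive Carob syrup twice a day or vitamin E"; vitamin E is taken once a day.
- **Total (Participants).** "The proposed sample size is 60 men with teratospermia and oligozoospermia", 30 per arm.
- **Blinding.** Staff who perform and analyse the semen, endocrine and "biomarker analysis (outcomes assessor) will be blinded to the participant grouping". No blinding of patients or recruiting staff is stated.
- **Recruitment.** It involves "a member of the research team (reproductive health researcher) and urologist present at" the clinic, and the investigators "will screen all the patients for the eligibility criteria at the time of admission".
- **List generation (Allocation).** "two 60- sets of random numbers will be created by a member of the research team not involved in recruitment".
- **Custody and use (Allocation).** Only the reproductive health researcher has access to the sequence. She puts the papers with the blocks of four into numbered envelopes. For each eligible man the researcher shuffles the envelopes, draws one and assigns.

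**The concern.** A permuted block of known size is predictable towards its end. Once two men in a block of four have received carob, the remaining places must be vitamin E. Anyone who knows the block size and sees earlier treatments can work this out without the list. Here the recruiting researcher has both: the products are visibly different, and she handles the blocks of four herself.

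The stake is selection bias in the primary comparison. Baseline semen results are available before allocation. A recruiter who knows the next arm can bring a man forward or hold him back, and with 30 men per arm a few such decisions could matter. The planned ANCOVA can adjust for measured baseline values if they are used as covariates, but not for unmeasured reasons for steering.

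**Working it through.** **Inputs.** Fifteen blocks of 4 (Allocation); 1:1 ratio (Intervention); 60 men (Participants). Assumptions for steps 1 to 5: blocks are used up in order, and the recruiter tracks past assignments.

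**1. The plan's own figure.** 15 x 4 = 60 allocations and 15 x 2 = 30 per arm. This agrees with the stated sample size.

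**2. Allocations known with certainty.** A 1:1 block of 4 has six equally likely orders.
- ABAB, ABBA, BAAB and BABA: only the fourth place is forced, so 1 certain.
- AABB and BBAA: the third and fourth places are forced, so 2 certain.

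Expected number per block = (4 x 1 + 2 x 2)/6 = 4/3. Share = (4/3)/4 = 33.3%. For block size 2m the share is 1/(m + 1); with m = 2 it is again 1/3.

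**3. Over the trial.** 15 x 4/3 = 20 of 60. Each block gives 1 or 2, so the minimum is 15 and the maximum 30. The count is 15 plus a binomial variable (15 trials, probability 1/3), and it lies between 16 and 24 with probability 0.989.

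**4. Best-guess accuracy.** Guess the arm used less so far in the block.
- Place 1: 1/2.
- Place 2: 2/3.
- Place 3: certain with probability 1/3, a coin toss with probability 2/3, so 1/3 + 2/3 x 1/2 = 2/3.
- Place 4: 1.

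Sum = 17/6, and (17/6)/4 = 70.8%, against 50% for simple randomisation.

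**5. Alternatives.** The fixed sizes are enumerated. The mixed sizes come from 4,000 simulated lists of 60 each, with a recruiter who knows the set of sizes but not their order.

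| Scheme | Certain | Best guess right |
|---|---|---|
| Fixed 4 | 33.3% (20 of 60) | 70.8% |
| Fixed 6 | 25% | 68.3% |
| Fixed 8 | 20% | 66.6% |
| Random 4/6 | about 5.5% (3.3 of 60) | about 69% |
| Random 4/6/8 | about 2.3% (1.4 of 60) | about 68% |

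The mixed-size lists in the table were cut off at 60. I also simulated 4,000 lists of sizes 4/6/8 built to close at exactly 60. Certain knowledge was about 2.4% (1.4 men) if the recruiter does not use the total. It was about 4.8% (2.9 men) if she knows that the list closes at 60 and counts down. The best guess was right about 68% of the time in both cases.

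**6. How far the figure depends on envelope use.** The text does not say clearly whether an envelope holds one assignment or a whole block.
- Single-assignment envelopes shuffled across all 60: the blocks dissolve. The expected forced run at the end is 2 x 30/31 = 1.9 men, and 1.9/60 = 3.2%.
- One envelope per block, read when opened: 3 of every 4 assignments, 75%, are known in advance.
- The recruiter consults the sequence she has access to: up to 100%.

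**The case against.** The strongest objection is that one third describes none of the readings of the procedure as written. Shuffling, whole-block envelopes and the recruiter's access to the list give about 3%, 75% or up to 100%. While the recruiter has the list, varying the block size achieves nothing. **This stands.** The 33.3% must carry its condition, and the change helps only together with custody outside recruitment and serial opening. The point does not disappear, however: serial use is what the stated aim of balance over time needs, and repairing only custody and envelope order would bring the block-size weakness fully into play.

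Second, the gain in best-guess accuracy is small, 70.8% to about 68%, and no bias in an outcome is estimated. **This stands.** The benefit lies almost entirely in the loss of certain knowledge.

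Third, fixed blocks of 4 give exactly 30/30, as intended. **This stands in part.** A mixed list built to total 60 also gives 30/30 at full recruitment.

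Fourth, numeric semen thresholds and the urologist's confirmation limit discretion. They limit who may enter but not when, and a baseline covariate cannot adjust for unmeasured reasons.

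Two stronger readings are tempting, and the text does not support them:
- A reader might infer from "two 60- sets of random numbers will be created by a member of the research team not involved in recruitment" that a spare allocation list exists. The words could equally mean inputs to one list, or be loose wording, and the next sentence describes only 15 blocks.
- A reader might infer that screening runs at one clinic three days a week, so that deferral is easy. The study setting also names a urology clinic, and the three days are tied to the run-in phase.

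**Conclusion.** The weakness is real, and its size is conditional. With one fixed block size of 4, blocks used in serial order and a recruiter who tracks earlier treatments, on average 20 of 60 allocations (33.3%, range 15 to 30) are certain in advance, and a best guess is right 70.8% of the time.

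That the recruiting researcher sees past treatments is inferred from three things: blinding limited to assessors, visibly different products, and her role in assigning. The article does not say open label. The inference is sound for her; it is not shown for the urologist. What patients know does not enter the arithmetic. Nor does the date of publication, since she knows the block size from her own task.

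The figure should not be read as the predictability of the procedure as now described. The recruiter's access to the sequence and the shuffling of envelopes are a separate and larger fault. Changing the block sizes is a low-cost improvement to make in the same revision.

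**What to change.** 1. Have the team member not involved in recruitment both generate and hold one 60-place list of randomly ordered block sizes, for example 4, 6 and 8, constrained to total 60 so that full recruitment gives 30/30.
2. Withhold the block sizes from recruiting staff and from public documents until recruitment ends. The size of 4 is already in print, so the new sizes should not be published in its place.
3. Have someone outside recruitment prepare envelopes that each hold a single assignment, and open them in serial order without shuffling.
4. Reconcile the wording on the two sets of random numbers with a single list, since 15 x 4 = 60 already covers the trial.

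Steps 1 and 3 must be made together; the change of block sizes alone gives no protection.

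**Cost.** A few lines of list-generation code, a change of wording, and the transfer of list custody and envelope preparation to the team member who already generates the numbers. No extra patients are needed. If recruitment stops inside a block, the arms may differ by a few men. Closing the list at exactly 60 costs a little concealment at the end (about 2.9 instead of 1.4 certain allocations, for a recruiter who counts down to 60).

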Allocation sequence will be password-protected and only accessible to the reproductive health researcher. She folds two times the paper containing 4-size blocks, put them in the standard thick envelopes and writes the serial numbers on them. All of the envelope will be kept at the recruitment center. Thus, for every eligible patient, the researcher randomly selects one of the envelopes after shuffling and assign subjects into intervention and comparison group.

**Data collection: **After physical examination and check baseline characteristic data and eligibility criteria, semen analysis and hormonal status, including serum follicle-stimulating hormone (FSH), prolactin, luteinizing hormone (LH), total testosterone and total antioxidant capacity (TAC) and malondialdehyde (MDA) will be done at baseline and 3 months after enrollment.

The semen samples will be collected in the privacy of a room near the laboratory after three days of sexual abstinence and kept at 37°C. A validated and standard laboratory (Fatemezahra Infertility Center) will be used for collection and analyses of the semen. Sperm characteristics will be studied on fresh samples immediately after collection. After liquefaction seminal fluid at room temperature, routine semen analyses including semen volume, concentration, sperm motility and morphology will be performed according to WHO recommendation (14). 

Blood samples will be centrifuged and serum will be stored at -50°C for metabolomics biomarkers that include oxidative stress index and sex hormones. Measuring the sex hormones is done by ELISA method and according to instruction of the related kit.

**Participant timeline: **The time schedule of enrolment, interventions, and assessments based on SPIRIT 2013 template (15) has been shown in Table 1.

**Table 1 T1:** SPIRIT 2013 schedule of enrolment, interventions, and assessments

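### The only holder of the allocation sequence is a role that also screens patients and fills and numbers the envelopes, so the stated mechanism does not conceal allocation

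*Protocol article*

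**What the plan says.** All the relevant text is in the Methods of the protocol article.

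- **Recruitment.** The clinic is staffed for recruitment by "a member of the research team (reproductive health researcher) and urologist present" three days a week. The investigators inform participants and "will screen all the patients for the eligibility criteria at the time of admission".
- **Eligibility criteria.** "The eligibility of each included subject will be confirmed by the urologist".
- **Allocation, generation.** Before the run-in phase, "two 60- sets of random numbers will be created by a member of the research team not involved in recruitment". Fifteen blocks of four are prepared, with A for carob and B for vitamin E.
- **Allocation, custody.** "Allocation sequence will be password-protected and only accessible to the reproductive health researcher". The next sentence, with the pronoun referring most naturally to that researcher, has her fold the papers that carry the blocks of four, place them in thick envelopes and number them serially.
- **Allocation, use.** "All of the envelope will be kept at the recruitment center". For each eligible patient the researcher shuffles the envelopes, takes one at random and assigns the patient.
- **Blinding.** Only those who perform and analyse the semen, endocrine and biomarker measurements are said to be blinded.
- **Intervention.** The arms are a syrup twice a day and vitamin E once a day. No dummy is described.

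**The concern.** Concealment requires that whoever can influence which patient enters, and when, cannot know or choose the next assignment. The plan starts in the right way, with a sequence "created by a member of the research team not involved in recruitment". It then gives sole access to that sequence to a role that recruits. A password does not hide a list from the one person who has the password, and a thick envelope does not hide its contents from the person who filled it.

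The setting adds to the exposure. Because the regimens look different and only the assessors are blinded, clinic staff can see what each earlier patient received.

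What is at stake is the comparability of the two groups at entry. Blinded laboratory reading limits bias in measurement and does nothing about who was enrolled into which arm. ANCOVA corrects only for prognosis captured by the covariates in the model. A positive result would be open to the objection that the men in the carob arm had a better outlook from the start, and that objection cannot be answered once enrolment is over.

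**Working it through.** **1. Trace of the roles**

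| Task | Who, according to the article | Stated or inferred |
|---|---|---|
| Generate the sequence | Team member outside recruitment | Stated |
| Hold the sequence | Reproductive health researcher only | Stated |
| Inform and screen patients | The investigators: reproductive health researcher and urologist | Stated, shared |
| Confirm eligibility | Urologist | Stated |
| Fill and number envelopes | Reproductive health researcher | Pronoun, natural reading |
| Keep envelopes | No keeper named; at the recruitment center | Place stated |
| Shuffle, draw and assign | The researcher | Natural reading; full label not repeated |

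The role label in the Recruitment paragraph and in the custody sentence is identical. One role therefore holds the list and takes part in screening. That conflict does not depend on the two inferred rows.

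**2. The envelope procedure against itself**

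- 15 blocks × 4 = 60, which matches the planned 60 men.
- If each paper carries one block of four, there are 15 envelopes for 60 men. If each envelope then serves four men, opening it for the first reveals the next three.
- If instead a fresh envelope is drawn for every man, 15 envelopes do not cover 60 men, and the order of use is no longer the order of the pre-generated blocked sequence. Serial numbers then have no function.
- On either reading, the shuffle and the draw are controlled by the person who filled and numbered the envelopes.

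**3. Predictability without the list (context)**

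Suppose blocks of four are used in order and past assignments are visible. There are six arrangements of AABB.

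- Known with certainty: position 4 always, and position 3 in 2 of the 6 arrangements. Per block this is 1 + 1/3 = 4/3. Over 15 blocks it is 20 of 60 (33%).
- Guessed correctly with the best strategy: 1/2 + 2/3 + 2/3 + 1 = 17/6 per block. Over 15 blocks it is 42.5 of 60 (71%).

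This is what a recruiter without the list could achieve. A recruiter who has the list, or who has opened a block paper, can know more.

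**4. Size of a possible bias (assumed shifts)**

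The article gives no figure for the shift, so a range is shown. Inputs: n = 30 per arm and two-sided α = 0.05 (article); prognosis shift δ in SD units (assumption). For example, 6 of 30 men in one arm replaced by men 1 SD better gives 6/30 × 1 = 0.2 SD.

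With no true effect, the two-sample t statistic is noncentral t with 58 degrees of freedom and noncentrality δ√(n/2) = δ√15. The critical value is 2.002.

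| δ (SD) | δ√15 | Share of target d = 0.70 | Two-sided rejection rate |
|---|---|---|---|
| 0 | 0 | 0% | 5.0% |
| 0.1 | 0.387 | 14% | 6.7% |
| 0.2 | 0.775 | 29% | 11.9% |
| 0.3 | 1.162 | 43% | 20.8% |

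**5. What ANCOVA could remove**

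Simulation with 30 per arm and no treatment effect, assuming a baseline–outcome correlation of 0.7 and steering only through the measured baseline value, shifted by 0.4 SD. The shift carried to the outcome is 0.4 × 0.7 = 0.28 SD. The rejection rate is about 19% unadjusted and about 5% with ANCOVA on that baseline. The rates in step 4 therefore apply only to the part of a shift that the model does not adjust for.

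**The case against.** Five points can be made for the plan.

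**The shuffle.** A reader might infer that all 60 assignments are known to the recruiter in advance. The text does not support that. If the shuffle and random draw are carried out honestly, the list shows what each block contains and not which block comes next. This stands. What remains is that nothing enforces an honest draw, that the maker of the envelopes can recognise them, and that an opened block paper can reveal later assignments.

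**Other safeguards.** A reader might infer that nothing at all hinders steering. That is too strong. The generator is outside recruitment, the urologist confirms each man's eligibility, written consent precedes enrolment, and the papers are folded twice inside thick envelopes. These count, but only in part. The researcher still helps to inform and screen patients and can influence who is approached and when.

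**Inferred roles and labels.** The article never calls the trial open-label; this is inferred from assessor-only blinding and the differing regimens. The assigner is called only the researcher, and no keeper of the envelopes is named. These are fair readings and should be marked as such.

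**The planned analysis.** The 12% and 21% rates come from an unadjusted t-test with assumed shifts, whereas the plan specifies ANCOVA. Steering on visible baseline semen values would be largely removed if those values are the covariates, which the article does not specify. So these rates are not a forecast for the planned analysis.

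**A condensed article.** A fuller document may say more. However, the article does not leave this mechanism out. It states who holds the list and how the envelopes are made and used, and what it states does not conceal allocation.

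**Conclusion.** The point holds as a conflict of roles combined with an unsound envelope procedure. The sequence is accessible only to a role that also screens patients. That role fills and numbers the envelopes and, on the natural reading, draws them. The papers carry whole blocks, and the shuffle for each patient conflicts with a pre-generated, serially numbered sequence. Selection at enrolment is possible; the article does not show that it will occur.

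The size cannot be derived from the article. On the assumption of a 0.2 to 0.3 SD shift in prognosis that ANCOVA does not remove, the false-positive rate would be about 12% to 21% instead of 5%. If steering acted only through adjusted baseline values, the rate could stay near 5%. The case for change does not rest on these figures. It rests on the trace of roles, and on the fact that lost concealment cannot be restored after enrolment.

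**What to change.** Replace all the custody and envelope sentences of the allocation paragraph, not only the one on access to the sequence. If only that sentence changed, the block papers and the random draw would remain and would contradict opening envelopes in numerical order. Suggested text:

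> The sequence is held only by the team member who generated it and who takes no part in recruitment, screening or assignment. That person prepares 60 opaque, sealed, sequentially numbered envelopes, each holding one assignment, in the order of the blocked sequence. The reproductive health researcher has no access to the list and opens the next envelope in numerical order only after eligibility and consent are recorded and the patient's number and date are written on it.

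Delete the shuffling, the random selection of an envelope and the papers that carry blocks of four.

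The cost is a change of wording and of who holds the list, plus 60 single-assignment envelopes. The non-recruiting team member is already in the plan, so no staff are added, and sample size and analysis are unaffected. The change has to be in place before the first patient is assigned.

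### Shuffling the envelopes and drawing one at random for each patient contradicts the planned blocks of 4: the scheme loses either balance over time or concealment, depending on what each envelope holds

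*Protocol article*

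**What the plan says.** All the steps stand in the Allocation section of the protocol article unless another section is named.

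- **Aim.** Block randomisation is chosen so that groups "result in equal sample sizes to ensure a balance across groups over time".
- **Blocks.** "15 blocks with size of 4 and combination of A for the carob and B for vitamin E group will be prepared". The random numbers are created by a team member who takes no part in recruitment.
- **Envelopes.** The sequence is then handed over: "Allocation sequence will be password-protected and only accessible to the reproductive health researcher". That person packs the envelopes: "She folds two times the paper containing 4-size blocks, put them in the standard thick envelopes and writes the serial numbers on them". Storage is on site: "All of the envelope will be kept at the recruitment center".
- **Use.** Finally, "for every eligible patient, the researcher randomly selects one of the envelopes after shuffling".

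The Recruitment section places the same role at the point of entry: "a member of the research team (reproductive health researcher) and urologist present at Fatemezahra Infertility Clinic 3 days in a week". The Blinding section covers only those who perform and analyse the outcome measurements. The Intervention section gives syrup twice a day in one arm and vitamin E once a day in the other.

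**The concern.** A block list balances the arms over time only if its assignments are used in the listed order. Serial numbers on envelopes exist to fix that order, and a shuffle before each draw discards it. The article therefore prescribes a blocked sequence and then a step that does not follow it.

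The description of the envelopes adds a second difficulty. The folded paper is said to contain the blocks of 4, which suggests a whole block in each envelope. That would give 15 envelopes, although the drawing step is written per patient for 60 patients. A paper with a whole block on it also displays assignments that have not yet been made.

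At stake are the stated balance over time and, more seriously, concealment. The people who screen and enrol work where the envelopes are kept. If an assignment can be seen ahead or a draw put back, the decision to enrol a man can depend on the arm he would enter. The planned ANCOVA cannot repair selection that acts through unmeasured factors.

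**Working it through.** **Inputs (protocol article).** 15 blocks of size 4, two arms A and B, 1:1 allocation, 60 men with 30 per arm, and one random draw after shuffling for each patient.

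**The plan's own figure.** 15 × 4 = 60 patients and 15 × 2 = 30 per arm. The block scheme reproduces.

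**Benchmark: blocks of 4 used in order.** After 30 patients, 7 blocks are complete (28 patients, 14:14) and 2 patients belong to the eighth. The difference between arms is 0 or 2, so P(difference > 2) = 0. The running difference never exceeds 2 at any point.

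**Reading 1: one assignment per envelope, shuffled and drawn without replacement.** The number of A among the first 30 is hypergeometric (60 envelopes, 30 of them A, 30 drawn).

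- Var(A) = 30 × ½ × ½ × (30/59) = 3.81, so the SD of A − B is 2 × √3.81 = 3.9.
- P(A = 15) = C(30,15)² / C(60,30) = 0.203. P(A = 14) + P(A = 16) = 0.358. P(difference > 2) = 1 − 0.203 − 0.358 = 0.439.
- P(A = 13) + P(A = 17) = 0.243. P(difference ≥ 6) = 0.439 − 0.243 = 0.196.
- Four consecutive patients split 2:2 with probability C(30,2)² / C(60,4) = 189,225 / 487,635 = 0.388, against 1.00 with intact blocks.
- In 20,000 simulated sequences the largest running difference averaged 6.3 (95th percentile 10), against a maximum of 2 with blocks.
- All 60 envelopes are used in the end, so the final split is exactly 30:30.

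**Reading 2: one whole block per envelope, used for four consecutive patients.** Shuffling whole blocks leaves each group of four at 2:2, so balance survives. Opening the paper for the first patient shows the other three: 3/4 of assignments, or 15 × 3 = 45 of 60, are known in advance. This reading does not fit the per-patient wording of the draw.

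**Reading 3: one whole block per envelope, redrawn for every patient, next unused letter taken.** In simulation 39.7% of groups of four split 2:2, and the largest running difference averaged 5.9. Each opened paper shows the other letters of its block, though not necessarily those of the next three patients.

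**Reading 4: one whole-block envelope used up per patient.** The 15 envelopes run out after 15 of 60 patients.

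None of these four readings keeps both the blocking and the concealment.

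**After the fix.** With one assignment per envelope opened in serial order, all 15 groups of four split 2:2, the running difference stays at 2 or below, the final split is 30:30, and no unopened assignment is displayed.

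**Side calculation on fixed blocks.** For someone who knows that the block size is 4 and sees past assignments, the fourth assignment is always certain and the third is certain when the first two agree (probability 1/3). The certain share is (1 + 1/3) / 4 = 1/3, about 20 of 60.

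**The case against.** The strongest reply is that the harm is smaller than it looks.

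- **The draw in Reading 1 is still valid randomisation, ends at 30:30, and is less predictable than fixed blocks of 4 if done honestly.** This stands. Only balance over time is lost, and no interim analysis is described for which a mid-trial imbalance would matter directly. It matters only if patients or measurements drift over the recruitment period, which the article does not show. The exposure to bias under this reading comes from re-drawing, not from foresight.
- **The two harms need different readings.** This stands. A reader might infer that the shuffle both destroys the blocks and reveals the next three assignments. The text does not support the two together in full: the next three are shown for certain only when one envelope serves four consecutive patients, and then the block balance is intact. The figure of 45 of 60 belongs to that reading alone.
- **The envelope sentence is unclear English and may mean block lists cut into single slips.** This is possible, and it leads back to Reading 1. Shuffling only the four envelopes of the current block would preserve balance, but nothing in the text confines the shuffle in this way.
- **Serial numbers and a stored sequence allow some checking.** This stands. A reader might infer that the allocation cannot be audited at all. Used numbers could be compared with the list, and the article does not say whether draws are logged. What can be said is that, without a fixed order of use, a returned envelope is easier to hide.
- **A fixed block size of 4 is no error.** Agreed. It contradicts nothing in the article and is only a matter of further protection.

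The contradiction itself is untouched by these points. It lies in steps that the article spells out, so it is not a detail left to a fuller document.

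**Conclusion.** The concern holds as an internal contradiction in a stated rule: blocks of 4 intended for balance over time, followed by a shuffled draw for every patient.

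The size depends on what an envelope holds. With one assignment each, the chance of a difference above 2 after 30 patients is 44% (20% for 6 or more) instead of 0, with the final 30:30 unaffected. This assumes draws without replacement from 60 envelopes. With a whole block each, used for four consecutive patients, up to 45 of 60 assignments are known in advance while balance is kept. The article does not settle which applies.

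Restoring serial order is not enough on its own. The reproductive health researcher holds the list, packs the envelopes and is present at recruitment, so strict serial order would let that person know every assignment. The order of use and the holder of the list have to be corrected together, before patients are allocated.

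**What to change.** Rewrite the Allocation section as follows.

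1. Delete the shuffling and the random selection of envelopes.
2. Use 60 opaque, sealed, serially numbered envelopes with one assignment each.
3. Open them strictly in serial order, and only after the patient's ID and the date have been written on the sealed envelope.
4. Have the list held and the envelopes packed by the non-recruiting team member who already generates the sequence, and not by the reproductive health researcher.
5. Optionally, vary the block sizes at random (for example 4 and 6) and do not disclose them to those who recruit. This is worth considering because only outcome assessors are stated to be blinded and the regimens differ, so past assignments may be apparent at the clinic.

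The cost is 60 envelopes instead of 15 (if whole blocks were meant), a regenerated list, and the transfer of list-holding and packing to an existing team member. Sample size, visits and analysis are unaffected.
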